### Eligibility criteria

The inclusion criteria are: (1) aged 18 years and above; (2) postinjury <6 months; (3) cervical or thoracic incomplete SCI; (4) able to sit without support for 30 s and (5) sufficient upper-limb function to voluntarily perform arm cycling movement on a stationary arm bike, with or without use of gripping aids.

The exclusion criteria are: (1) ongoing issues with shoulder instability or shoulder pain; (2) contraindications to exercise in an upright posture (eg, postural hypotension, unresolved pressure ulcer, uncontrolled cardiovascular conditions); (3) pregnancy and (4) unable to understand explanation of the study and/or instructions of the intervention.

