### Interventions

All participants will receive standard in-patient rehabilitation care at the spinal unit. The ACET group will additionally undertake 8 weeks of progressive, unsupervised ACET with a stationary arm bike (MagneTrainer ER).

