#### Primary outcome measure

The primary outcome of the study is trunk control, assessed by:

*1. Volitional control of the trunk*

*Static and dynamic sitting balance*. Sitting balance will be assessed using the following tasks: unsupported sitting for 30 s, forward and lateral reaching,^12 43^ bilateral voluntary arm raise^44^ and rapid shoulder flexion.^12^ Participants will perform each task five times while seated on a plinth with their trunk unsupported, feet flat on the floor, hips and knees positioned at 90°, and the popliteal fossa approximately a palm’s width away from the edge of the plinth.

For the unsupported sitting task, participants will be instructed to sit unsupported as stable and upright as possible for 30 s (figure 2A). For the multidirectional reaching tasks (figure 2B and C), participants will be asked to sit in an upright position and use the less affected arm to reach forward and to the side as far as possible without losing balance. For the voluntary arm raise task (figure 2D), participants will be instructed to hold a resistance band with both hands and move the band up by flexing the shoulder joints to the maximum active range of motion. A rapid shoulder flexion task will be used to assess anticipatory and compensatory postural adjustments, whereby participants will, while sitting, raise their arms to a horizontal outstretched position as quickly as possible in response to a short, sharp verbal cue (figure 2E). Movement of the upper limbs and trunk will be captured in 2D videos recorded with a camera in 1080 p at 30 frames per second (iPad mini fifth generation, Apple, CA, USA). The camera will be placed at the angle perpendicular to the movement plane. Furthermore, the kinematics of the trunk will be recorded at 100 Hz using an inertial measurement unit (IMU)^45^; (Sessantaquattro+, OT Bioelettronica, Turin, Italy) placed at the fourth thoracic spinous process (figure 3). Sitting posture (spinal curvature at rest),^46^ reaching distance,^12^ angular displacement of the trunk^47^ and range of motion of the shoulder joints^44^ will be analysed from the 2D videos.

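### Shoulder range of motion is listed, unranked, among the measures of the primary outcome trunk control, so a gain confined to the arms could be reported as better trunk control

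*Protocol article*

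**What the plan says.** The section Primary outcome measure opens with "The primary outcome of the study is trunk control, assessed by" and then sets out two parts: volitional control of the trunk, and the neurophysiological mechanisms behind it.

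The first part uses five seated tasks and four video variables: sitting posture, reaching distance, trunk angular displacement and, last, "range of motion of the shoulder joints^44^ will be analysed from the 2D videos". No variable is placed above another and no composite is described. The shoulder variable matches the arm-raise task, in which participants hold a resistance band and "move the band up by flexing the shoulder joints to the maximum active range of motion". The caption of Figure 2 presents that task, with the others, as an assessment of volitional trunk control.

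Trunk-specific recordings sit under the same primary outcome. In the first part, "the kinematics of the trunk will be recorded at 100 Hz using an inertial measurement unit" at T4. In the second part come high-density EMG of the erector spinae during the seated tasks, and evoked potentials in the same muscle.

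Three other sections bear on the point:
- Interventions: "The ACET group will additionally undertake 8 weeks of progressive, unsupervised ACET with a stationary arm bike".
- Eligibility criteria: the population is "cervical or thoracic incomplete SCI".
- Study population and sample size: the calculation speaks of one primary outcome measure and takes its effect size from trunk angular displacement in forward reaching.

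Statistical analyses applies a 0.05 level to every test and does not say which variable decides the primary question.

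**The concern.** Shoulder range of motion describes the limb that the intervention trains, not the trunk. Some participants with cervical injury may start with reduced active shoulder range. Eligibility requires only enough upper-limb function to turn the crank, and gripping aids are allowed. If eight weeks of cranking strengthens their shoulders, the band goes higher whether or not the trunk has recovered. Only the ACET group has this extra training, so a local arm effect would differ between the groups and would favour ACET.

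The trial's first objective concerns sitting balance, and its stated aim is volitional control of the trunk. As the outcome section is written, a significant group difference in shoulder range would be a positive finding on a variable classed as primary evidence of trunk control. This is separate from the number of primary variables. Adjusting alpha would lower the chance of a spurious difference, but it would not turn a true shoulder difference into a trunk difference.

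**Working it through.** **1. What the sample size rests on.** Inputs from Study population and sample size: d = 0.85, independent t-test, 80% power, 5% significance. Sidedness is not stated.

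- Normal approximation: n per group = 2(1.960 + 0.842)² / 0.85² = 15.70 / 0.7225 = 21.7, so 22.
- Exact two-sided calculation (noncentral t): 22.73, so 23 per group and 46 in total. Power at 23 per group is 80.5%.
- One-sided: 17.83, so 18 per group.

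The stated 46 is reproduced by the two-sided t-test. It belongs to trunk angular displacement in forward reaching, so the protocol already has a trunk-derived variable for which it is sized.

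**2. The sections side by side.** The sample size section treats one trunk variable as the primary measure. The outcome section puts that variable in an unranked list with shoulder range of motion. The statistical section tests outcome measures at 0.05 each. Nothing in the three prevents shoulder range alone from supporting the trunk-control conclusion.

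**3. What an arm-only effect would do.** The document gives no effect of cranking on shoulder range, so d is assumed here. With n = 23 per group and two-sided 0.05, the noncentrality is d × √(n/2) = d × √11.5 = 3.391d.

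| Assumed effect on shoulder range | Noncentrality | Chance shoulder range is significant | Chance trunk angle is significant, no trunk effect |
|---|---|---|---|
| d = 0.3 | 1.02 | 17% | about 5% |
| d = 0.5 | 1.70 | 38% | about 5% |
| d = 0.85 | 2.88 | 80% | about 5% |

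The third column is ordinary t-test power. It shows what follows if such an effect exists and says nothing about whether it does. The value 0.85 is the protocol's figure for trunk angle, used only as an upper case; nothing links it to the shoulder. The useful contrast is with the last column: if trunk angle decides, an arm-only effect of any size leaves the false-positive rate near 5%.

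**4. Reaching distance is a different case.** Participants "use the less affected arm to reach forward and to the side as far as possible without losing balance", seated with the trunk unsupported. The reach is limited by balance, and the better arm is used. Arm excursion can contribute, but the task depends on the trunk in a way that active shoulder range does not.

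**The case against.** The strongest reply is that the protocol never says trunk control is scored from these variables. There is no composite and no rule that any one significant variable suffices. The sample size section points to trunk angular displacement as the primary measure. The T4 sensor and the erector spinae recordings sit under the same primary outcome, so an arm-only effect could show itself as a shoulder gain with no trunk change. A full analysis plan, not shown, may name the deciding variable. The arm raise is bilateral, resisted and done without trunk support, so it is not purely an arm task. The eligibility criteria also exclude ongoing shoulder instability or pain and require enough arm function to cycle, which limits how impaired the shoulders can be.

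Most of this stands, and it rules out stronger readings. A reader might infer that an arm-only effect would be reported as improved trunk control; the text supports only that it could be. A reader might also infer that reaching distance is equally unsuitable, or that participants with thoracic injury already have full shoulder range and so cannot improve on it. The conditions of the reaching task argue against the first, and the document has no baseline shoulder data to support the second.

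The reply does not remove the classification itself. The article places a shoulder-joint variable under trunk control, and no instruction requires it to be read against the trunk recordings. That is stated text, not a detail left to an analysis plan.

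**Conclusion.** The point holds for shoulder range of motion. It is listed as an unranked variable of the primary outcome, it measures a joint that only the ACET group additionally trains, and people with cervical injury, whose arms may be impaired, can enter. A gain confined to the arms could therefore be presented as primary evidence of trunk control, and the error would favour ACET.

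Its size cannot be derived from the document. The 17%, 38% and 80% figures are conditional on assumed shoulder effects. That cranking raises shoulder range without trunk change is a plausible mechanism which the protocol does not demonstrate. The point does not extend to dropping reaching distance, which is a legitimate sitting-balance measure as performed here. The change is worth making because it is cheap and closes a route to a misleading primary conclusion.

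**What to change.** In Primary outcome measure:

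- Name trunk angular displacement during forward reaching as the variable that decides the trunk-control claim. The sample size already rests on it, so 23 per group before dropout is unchanged.
- Move shoulder range of motion to a secondary upper-limb outcome, and state that it is not by itself evidence of trunk control.
- For the arm raise, report trunk motion during the lift, from the T4 sensor or the video.
- Keep reaching distance as a sitting-balance measure, and state that it will be interpreted together with trunk angle.

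The cost is a wording change and a different read-out of files already planned. It needs no new visits, equipment or participants. The one small loss is that shoulder range of motion no longer counts as primary evidence.

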**Figure 2 F2:**
[figure not shown]
Assessment of volitional trunk control. (**A**) Unsupported sitting for 30 s; (**B**) forward reaching; (**C**) lateral reaching; (**D**) bilateral voluntary arm raise and (**E**) rapid shoulder flexion in response to a verbal ‘Go’ cue.

**Figure 3 F3:**
[figure not shown]
Setup of high-density surface electromyography. An inertial measurement unit (IMU) is placed at the 4th thoracic spinous process (**T4**) and an electrode grid is placed over the erector spinae parallel to the thoracic spine, with the top of the grid placed two centimetres laterally from the 12th thoracic spinous process (**T12**).

*2. Trunk control neurophysiological mechanisms*

*Neuromuscular control of the trunk*. Muscle activity of trunk muscles during seated balance tasks, as measured with high-density surface electromyography (HDEMG). Activity of the lumbar ES during seated balance tasks (figure 2) will be recorded using HDEMG which contains multiple small electrodes in a large electrode grid. HDEMG is a non-invasive technique and provides a topographic representation of muscle activity.^48 49^ This methodology is suitable for investigation of neuromuscular function of paraspinal muscles (ie, ES) which have multiple muscle fibres covering several levels of the spine and are innervated by multiple spinal nerves from the adjacent spinal levels.^50^ EMG recording from a larger area of the ES, as opposed to the bipolar EMG, may capture changes in regional distribution of activation across the spinal levels of the ES, providing new knowledge of recovery of trunk muscles in humans with SCI. Semi-disposable HDEMG grids (HD08MM1305, OT Bioelettronica) consisting of 64 oval-shaped electrodes arranged in 13 rows by 5 columns, minus the top left corner (figure 3; 1 × 1.5 mm electrode, 8 mm interelectrode distance), will be used to record lumbar ES activity. An adhesive foam (FO108MM1305, OT Bioelettronica) will be attached to the grid and its cavities will be filled with conductive paste (AC Cream, Spes Medica, Genoa, Italy). The skin over the muscle belly will be shaved, gently abraded with paste (Nuprep Skin Prep Gel, Weaver and Company, CO, USA), and cleaned with water to remove any residue from the paste. The grid will be placed on the ES in parallel with the lumbar spine, with the top edge of the grid placed 2 cm away from the centre of the 12th thoracic spinous process, and the bottom edge extended in the caudal direction to approximately the 4th lumbar spinous process (figure 3). One reference electrode (Ambu WhiteSensor WS, Ballerup, Denmark; 36 mm × 40 mm) will be placed on the seventh cervical spinous process and connected to the Sessantaquattro+, and a second ground electrode will be placed unilaterally over the iliac crest for a bipolar EMG system placed on the deltoid. An adhesive electrode (19.8 mm × 35 mm) of a bipolar EMG system (Delsys Bagnoli-2 EMG system) will be placed on the muscle bellies of the anterior deltoid (AD) of the less affected arm to record AD activity during the arm raised task. HDEMG will be recorded in monopolar mode with an amplifier (256 V/V gain; Sessantaquattro+, OT Bioelettronica) and digitised at 2000 Hz using a 16-bits A/D converter (10–500 Hz bandpass filter, input resistance 100 kΩ). Bipolar EMG (pre-amplified x1,000, band-passed filtered 20–450 Hz) will be recorded simultaneously via an isolated auxiliary input device (ISO-AUXSP, OT Bioelettronica), operating a 0.5 V/V gain alongside HDEMG using OT Biolab software (OT Bioelettronica) and stored in a local computer for postprocessing purposes. Root-mean-square (RMS) amplitudes and the centroid of RMS activation of the lumbar ES will be analysed.

*Corticospinal axons excitability of the ES*. To assess the excitability of the corticospinal axons projecting to the ES, high-voltage electrical stimulation (Digitimer stimulator, DS7AH, UK; square wave pulse, pulse duration 200 μs) will be applied at the cervicomedullary junction to elicit motor evoked potentials (CMEPs) in the ES^16 51^ when participants are seated in their preferred comfortable position. Between 10 and 15 CMEPs will be recorded and averaged. Participants will be asked to relax initially, but the Jendrassik manoeuvre will be introduced to assess if little or no response in the ES is observed. The Jendrassik manoeuvre, where a participant will clench their teeth and flex fingers in a hook shape, has been shown to facilitate corticospinal excitability.^52^ Peak-to-peak amplitudes and latency of the averaged CMEP will be calculated.

#### Secondary outcomes

*3. Injury classification*

The American Spinal Injury Association Impairment Scale (AIS)^42^ grades (A to E) will be documented to determine any improvement in sensory/motor preservation after the intervention, relative to standard of care alone.

*4. Motor recovery*

Strength will be assessed by a physiotherapist using the ISNCSCI^42^ upper extremities motor score and lower extremities motor score.

*5. Neuropathic pain*

Neuropathic pain will be documented using the Neuropathic Pain 4 Questions (DN4) questionnaire that rates from 0 to 10, being ≥4 suggestive of neuropathic pain.^53^

*6. Physical and mental health*

Depression and anxiety will be assessed using the Patient Health Questionnaire (PHQ-9)^54^ and Generalised Anxiety Disorder (GAD-7),^55^ respectively. Each questionnaire rates from 0 to 21, with a classification of mild (0–5 points); moderate (6–10 points); moderately severe (11–15 points) and severe (15–21 points).

*7. Self-efficacy for engagement in exercise*

Participants will complete a modified version of the perceived competence scales (PCS),^56^ a short assessment of ACET self-efficacy, with responses indicated on a scale from 0 to 10, with 0 = no confidence and 10 = completely confident.

*8. Motivation for exercise engagement*

A modified version of the Treatment Self-Regulation Questionnaire (TRSQ)^57^—comprising 16 questions on a scale from 1 (not at all true) to 5 (very true)—will gauge a participant’s source of motivation for why they might want to engage in ACET (eg, to impress family or friends or to improve health). See online supplemental appendix 5 for the self-efficacy and motivation scales.

*9. Physical activity levels*

Free-living physical activity energy expenditure will be calculated from raw acceleration signals recorded using a wrist-worn accelerometer (GENEActiv) for prior to T1 and after T2. The device has been validated in wheelchair users,^58^ and participants will be instructed simply to wear the device continuously for 7 days. Additionally, to understand whether the early ACET may lead to a more active lifestyle in the long term, the Leisure Time Physical Activity in People with SCI questionnaire (LTPAQ-SCI) will be used at the follow-up to record the time spent performing moderate-to-vigorous-intensity leisure time physical activities.^59^ Research has shown that the number of minutes spent per week performing moderate-to-vigorous intensity activity is positively correlated with cardiorespiratory fitness.^60^ Pre-injury physical activity levels will be documented during the pre-intervention conversation. However, a more accurate measure of physical activity prior to the injury is not feasible to be collected as part of this study.

*10. Health-related quality of life*

The Short Form (SF-36) walk-wheel Health Questionnaire (V.2)^61^ includes eight scales, which together produce two main summary measures, each ranging from 0 to 100: physical health and mental health. The physical health measure includes scales of physical functioning, role-physical, bodily pain and general health. The mental health measure includes vitality, social functioning, role-emotional and mental health.^62^

*11. Independence*

The Spinal Cord Independence Measure (SCIM-III) scale^63 64^ will be assessed at admissions and discharge to indicate functional independence of the participants.

#### Qualitative methods

*12. Focus group*

We will conduct online semi-structured focus groups with a purposive sample of 15 participants from the ACET group to discuss the content and delivery of the intervention. Each group will have up to five participants and be moderated by an experienced qualitative researcher ([name]). We will explore participants’ expectations and experiences of the intervention, barriers and enablers to participation, and views on future implementation (online supplemental appendix 6). Discussions will be audio recorded and transcribed verbatim. The focus group recordings will be coded using Nvivo 9 software, analysed using a deductive thematic analysis^65 66^ and will be interpreted together with the quantitative data.

### Statistical analyses

Statistical analyses will be performed using the latest version of SPSS available at the time of analysis (IBM, Armonk, NY, USA). The distribution of the continuous variables will be tested for normality using the Shapiro-Wilk test and appropriate descriptive parameters will be reported and statistical tests will be applied accordingly. A mixed-model two-way repeated measures ANOVA, with group as the between-participant factor and time as the within-participant factor, will be used to compare outcome measures. This analysis will be performed according to the intention to treat approach. Post hoc tests will be applied where there is a main effect. Significance level will be set at 0.05 for all statistical tests. For the data that are normally distributed, effect sizes of partial eta squared (η2p) or Cohen’s d will be calculated. Additionally, potential confounders (eg, age, days since injury) will be included in the analysis. Subgroup analyses (eg, based on AIS classification) will also be performed if appropriate.

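### A Shapiro-Wilk test on the outcome variables selects the statistical test and governs effect-size reporting, with no named alternative and no rule for when it conflicts with the planned repeated-measures ANOVA

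*Protocol article*

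**What the plan says.** All of the relevant text is in the Statistical analyses section of the protocol article.

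- Pre-test: "The distribution of the continuous variables will be tested for normality using the Shapiro-Wilk test". The object tested is the variable itself; model residuals do not appear.
- Consequence of the pre-test: "appropriate descriptive parameters will be reported and statistical tests will be applied accordingly".
- Main model: "A mixed-model two-way repeated measures ANOVA, with group as the between-participant factor and time as the within-participant factor, will be used to compare outcome measures".
- Adjustment: "potential confounders (eg, age, days since injury) will be included in the analysis".
- Effect sizes: "For the data that are normally distributed, effect sizes of partial eta squared (η2p) or Cohen’s d will be calculated". Nothing is named for other data.
- Threshold: "Significance level will be set at 0.05 for all statistical tests".

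The abstract names only repeated-measures ANOVAs and Student's t-tests, so no distribution-free method is named anywhere. Strengths and limitations and the Randomisation section both state that participants and assessors are not blinded.

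**The concern.** This is a rule the article states, so it cannot be excused as detail left to an analysis plan. Three things are wrong with it.

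1. The outcome of a significance test on the trial data decides how those data are analysed. The quantity being compared (a mean difference, or a shift in ranks) is then not fixed until the data are in hand.
2. The pre-test sentence and the ANOVA sentence can point in different directions, and nothing says which governs. If the pre-test does, the group-by-time structure and the covariates could be lost for some outcomes and kept for others.
3. Reporting of an effect size depends on the pre-test. The sample size rests on a Cohen's d for trunk angular displacement in forward reaching, yet that same quantity is promised only if the variable passes. Bounded scores, such as the DN4 (0 to 10) and the PHQ-9 and GAD-7 (given as 0 to 21), are natural candidates to fail and so to be left without an estimate.

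At stake is whether readers can compare effects across a long list of outcomes, and whether the method can be seen to have been fixed in advance in an open-label trial.

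**Working it through.** **The plan's own figure.** The inputs from Study population and sample size are d = 0.85, 80% power, 5% level and an independent t-test. The two-sided noncentral-t solution is 22.73 per group, rounded up to 23, giving N = 46 with power 0.805. The stated 46 is reproduced and is used below as 23 per arm.

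**Chance that the switch fires on normal data.** If each arm is tested at 0.05, the chance of at least one rejection is 1 − 0.95² = 0.0975, about 10% per comparison. For k independent checks it is 1 − 0.95^k: 34% for k = 8, 46% for k = 12 and 64% for k = 20. Real checks share patients and are correlated, so these last figures are only illustrative.

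**Dependence on how the test is applied.** The article does not say whether the test is per arm or pooled. For a gamma variable with shape 4 (assumed), Shapiro-Wilk rejects in 34% of samples of 23 and 66% of samples of 46. For a lognormal with sigma 0.5 (assumed), it rejects in 60% and 90%.

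**Raw values against residuals.** Two equal subgroups, each normal, were pooled to n = 46. With subgroup means 0.85, 2, 3 or 4 SD apart (assumed), the raw variable is rejected in 4%, 7%, 33% or 86% of samples although the residuals are exactly normal. The distinction matters only for large gaps.

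**Effect of the two-stage rule on power and error.** The fallback is an assumption, since the article names none. The rule simulated is: Mann-Whitney if either arm fails Shapiro-Wilk, otherwise a linear model adjusted for baseline. There are 23 per arm, d = 0.85 and 3,000 runs per row, and the baseline correlation r is assumed.

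| Data | r | Switch rate | Adjusted model | Rank test | Two-stage rule | Change, two-stage minus adjusted |
|---|---|---|---|---|---|---|
| Normal | 0.4 | 0.106 | 0.858 | 0.792 | 0.853 | −0.005 |
| Normal | 0.6 | 0.094 | 0.927 | 0.766 | 0.914 | −0.013 |
| Normal | 0.8 | 0.103 | 0.997 | 0.774 | 0.974 | −0.023 |
| Lognormal, 0.5 | 0.4 | 0.843 | 0.855 | 0.910 | 0.911 | +0.056 |
| Lognormal, 0.5 | 0.6 | 0.827 | 0.919 | 0.909 | 0.920 | +0.001 |
| Lognormal, 0.5 | 0.8 | 0.828 | 0.991 | 0.904 | 0.917 | −0.074 |

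At an assumed d = 0.6 with normal data, power goes from 0.61 to 0.60 (r = 0.5) and from 0.78 to 0.75 (r = 0.7).

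With no true effect, the two-stage rule rejected in 0.045 to 0.050 of runs across the six rows. The Monte Carlo standard error is √(0.05 × 0.95 / 3000) = 0.004, so there is no sign of inflation.

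**Reading the sentences together.** The ANOVA sentence is unconditional. The pre-test sentence is conditional and names no alternative. The effect-size sentence is conditional and names nothing for the other case. No reading of the three fixes in advance what will be done, and reported, for a variable that fails.

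**The case against.** The other side has good arguments.

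- **The fallback is not in the text.** The article never mentions a rank test, single-visit tests or dropping covariates. It says that the ANOVA will be used and that confounders will be included. Transforming the variable and running the same ANOVA would fit the wording equally well. This stands: loss of the adjusted model is possible, not planned. A reader might infer that adjustment is lost every time the pre-test fires; the article does not say so.
- **Cohen's d is named.** A reader might infer that only partial eta squared would be given, which is not a between-arm difference. The effect-size sentence offers Cohen's d as well, so that inference fails. What remains is the condition on normality. Strictly, the sentence does not forbid an effect measure for other data; it just promises none.
- **Larger numbers do not measure the rule.** Counting 5 tasks × 4 visits × 2 arms gives 1 − 0.95^40 = 87% for at least one flag. The article does not specify testing by cell, the cells are not independent, and one flag would not switch the whole analysis. Likewise, at d = 0.6 one can contrast an adjusted model (0.62 to 0.78 for r = 0.5 to 0.7) with a rank test (0.48). That applies only when the switch fires, and an unadjusted t-test already has about 0.51, so nearly all the drop comes from losing the baseline.
- **The switch is sometimes harmless or helpful.** With skewed data and weak baseline correlation the rank test did better (0.910 against 0.855).
- **Pooling matters little for modest subgroup differences,** with 4% to 7% rejection up to a gap of 2 SD.

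These points limit the size of the concern. They do not supply a rule for which sentence governs, or an estimate for outcomes that fail.

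**Conclusion.** The point holds in a limited form. The article lets a normality test on the observed variables decide the method and condition the effect size, beside an unconditional commitment to an ANOVA, and it does not reconcile the two. The primary harm is a method that can be chosen after seeing the data in an unblinded trial, together with selective reporting of effect sizes.

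The cost in operating characteristics is modest under the assumed fallback. With normal data and 23 per arm, about 10% of comparisons switch by chance, average power falls by about 1 to 3 points, and type I error is not clearly inflated. With the assumed lognormal data, the change ran from a gain of about 6 points to a loss of about 7, depending on the baseline correlation. The distributions, correlations and fallback are all assumptions; only d = 0.85, 23 per arm and the 0.05 level come from the article. A claim of inflated false-positive rates, or of a large certain loss of power, is not supported.

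**What to change.** Amend the Statistical analyses section, and any analysis plan, as follows.

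1. Remove the Shapiro-Wilk test as the selector of the analysis.
2. Name one model in advance for each continuous outcome: the planned mixed model, or a model adjusted for the pre-randomisation value, with its covariates listed.
3. Judge the model's assumptions on its residuals.
4. Pre-name a sensitivity analysis on the same model, either a stated transformation or a bootstrap or permutation analysis.
5. Report the adjusted between-arm difference with a 95% CI for every outcome, whatever its distribution. Standardised effect sizes can be added.

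The cost is wording only. The stated sample size of 46 evaluable participants, the visits and the data collected do not change.
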